### Risks and Potential Benefits

Currently, pimavanserin only has the indication of hallucinations and delusions associated with Parkinson's disease psychosis. Hence, in Sub-Sero, we will use pimavanserin *off-label*. We believe that pimavanserin in monotherapy holds promise as an alternative new treatment option to conventional antipsychotic medication in patients with schizophrenia spectrum disorders. Thus, in despite of the fact that the drug will be used off-label, we believe that the known side-effects of pimavanserin will be markedly milder than those of conventional antipsychotic medication. In particular, the risks of extrapyramidal symptoms (EPS) and hyperprolactinemia are limited with pimavanserin (Robinson et al., 2005).

No interim analyses will be performed. Instead the open label design permits a continuous evaluation of potential side-events and the overall safety of the study. Patients will be monitored closely by the study physicians and nurses, and side-events will be reported to the Danish Medical Authorities through an electronic report system. The study will be monitored closely by GCP throughout the study period.

By participating in Sub-Sero, patients will undergo more comprehensive testing, scans, and examinations than if undergoing treatment in a conventional regional mental health setting. Although this examination program may be burdensome for some patients, the thorough examinations may also be viewed as a potential benefit.

### Outcome Measures and Analysis Methods

#### Primary Endpoint

The primary clinical endpoint will be reduction in the PANSS positive subscale score [PANSS positive baseline - PANSS positive at week 6].

#### Secondary Endpoints

Secondary clinical endpoints include reduction in PANSS positive subscale score compared to baseline by week 2 and 4, respectively. Also, we will explore effects on negative, obsessive symptoms, sexual functioning, as well as the proportion of patients achieving symptomatic remission (Andreasen criteria) at week 6 (Robbins et al., 1994).

Secondary neuropsychiatric endpoints comprise in-depth characterization pre-treatment predictors of symptom reduction. Measurements will comprise cerebral serotonin 2AR binding potential, cognition, thalamic glutamate levels, blood test, and genetic analyses. After 6 weeks, also the degree of 2AR occupancy in patients, as indexed by plasma-pimavanserin, will be determined.

## Anticipated Results

### Sample Size Calculation

In Sub-Sero, we hypothesize that treatment with pimavanserin will have a similar clinical effect as was observed in a previous, comparable cohort in which patients underwent 6 weeks of treatment with amisulpride. Neurobiologically, we expect psychotic symptom reduction after pimavanserin treatment to be most prominent in patients with low frontal serotonin 2AR binding potential at baseline.

Our previous amisulpride cohort comprised 46 initially antipsychotic-naïve, first-episode schizophrenia patients. Details on the cohort are provided in, e.g. (Nielsen et al., 2012a; Nielsen et al., 2012b; Nielsen et al., 2016; Wulff et al., 2019). The 6 weeks of treatment with amisulpride, a dopamine D2R/D3R antagonist [with serotonin 7, but not serotonin 2A affinity (Abbas et al., 2009)], produced a mean reduction in PANSS positive score of 5.98 with a standard deviation of 4.68 (**Figure 1**). We have estimated a “trial effect” (or natural variation) to a reduction in PANSS positive to 2.5. With 46 patients treated with amisulpride for 6 weeks, the observed power was 95%.

**Figure 1 f1:**
[figure not shown]
Treatment response, amisulpride. Historical data from our group showing changes in PANSS positive symptoms in an independent cohort of 46 antipsychotic-naïve, first-episode schizophrenia patients treated with amisulpride (mean dose of 279.4 mg/day) monotherapy for six weeks. Details on the cohort have previously been published, e.g.(Nielsen et al., 2012a; Nielsen et al., 2012b; Nielsen et al., 2016; Wulff et al., 2019).

We have used these effect estimates in our sample size calculation for the Sub-Sero. Thus, when setting the desired power to 80% and the significance level of a=0.05, the needed sample size for Sub-Sero is 29 patients completing 6 weeks of pimavanserin treatment.

In our previous cohort, the attrition rate was 25%. Assuming a similar attrition rate of 25% in Sub-Sero, we aim to include 40 patients at baseline. In order to secure power in Sub-Sero, we will continue inclusion of patients until 30 patients have completed 6 weeks follow-up examinations.

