## Methods

### Study Design

One-armed, open label, investigator-initiated, proof-of-concept trial.

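### The 29 completers and the 95% power at 46 do not follow from a one-arm test of 5.98 against the 2.5-point trial effect; the role of 2.5 and the null value need to be fixed

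*Protocol article*

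**What the plan says.** Under Study Design the trial is a "One-armed, open label, investigator-initiated, proof-of-concept trial". The Primary Endpoint section reads "The primary clinical endpoint will be reduction in the PANSS positive subscale score [PANSS positive baseline - PANSS positive at week 6"; it names no reference value for that reduction.

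The Sample Size Calculation reports that six weeks of amisulpride "produced a mean reduction in PANSS positive score of 5.98 with a standard deviation of 4.68". It then gives an estimated trial effect ("or natural variation) to a reduction in PANSS positive to 2.5") and adds: "With 46 patients treated with amisulpride for 6 weeks, the observed power was 95" per cent.

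After Figure 1 the text says that these effect estimates were carried into the calculation. The error rates are given as 80% power and a significance level of 0.05, and the result reported is that "the needed sample size for Sub-Sero is 29 patients completing 6 weeks of pimavanserin treatment". On dropout it says: "Assuming a similar attrition rate of 25% in Sub-Sero, we aim to include 40 patients at baseline". Inclusion continues until 30 patients have completed week 6.

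The sidedness of the test, its null value, and whether 2.5 is a null, a difference to detect or an amount to subtract are not stated.

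**The concern.** In a one-arm, open-label trial, some of the fall in the PANSS positive score will come from taking part, from the natural course and from regression towards the mean. The 2.5-point trial effect is the protocol's only stated figure for that non-drug change. The natural use of the inputs is therefore to test an expected 5.98 against a background of 2.5. The published 29 and 95% do not match that test.

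The mismatch matters because the null value decides what a positive result would mean. A mean reduction clearly above 2.5 suggests something beyond participation. A mean reduction clearly above zero does not, since the authors themselves expect 2.5 points without a drug effect.

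**Working it through.** **Inputs** (Sample Size Calculation): mean reduction 5.98, SD 4.68, trial effect 2.5, alpha 0.05, power 80%, stated results 29 completers and 95% at 46. Sidedness is not given; I assume two-sided. The one-sided versions of the calculations below do not reproduce both figures.

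**Formulas.** With z₀.₉₇₅ + z₀.₈₀ = 1.960 + 0.842 = 2.802:
- one sample: n = (2.802 × SD / δ)²
- two groups: n per group = 2 × (2.802 × SD / δ)²

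The t-test figures use the noncentral t distribution.

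**Which δ reproduces the plan's figures?**

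| Calculation | n for 80% (normal / t) | Power at 46 (normal / t) |
|---|---|---|
| Stated in the protocol | 29 | 95% |
| One sample, δ = 2.5 | 27.5 → 28 / 30 | 95.2% / 94.3% |
| Two groups, δ = 5.98 − 2.5 = 3.48 | 28.4 → 29 / 30 per group | 94.6% / 94.2% (46 per group) |
| One sample, δ = 3.48 | 14.2 → 15 / 17 | 99.9% / 99.9% |
| One sample, δ = 5.98 | 4.8 → 5 / 7 | over 99.9% |
| Two groups, δ = 2.5 | 55.0 → 56 / 56 per group | 72.6% / 71.7% |
| Two groups, δ = 5.98 | 9.6 → 10 / 11 per group | over 99.9% |

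Two rows come close to both stated figures.

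- **One sample, δ = 2.5.** This makes the background change itself the difference to detect. The same arithmetic would also describe a 2.5-point shortfall from 5.98, that is, 5.98 against 3.48, but the text does not state that aim.
- **Two groups, δ = 3.48.** This uses all three inputs and gives exactly 29 by the normal formula. It supposes a second group of equal size with the same SD that shows only the trial effect. Sub-Sero has one arm, and 2.5 is a fixed estimate.

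**Power of the one-arm test against 2.5.** δ = 3.48, SD 4.68, t test: 97.2% at 29 and 97.6% at 30. If the benchmark were 3.5, δ = 5.98 − 3.5 = 2.48, and power at 30 is 80.1%.

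**Conditional check: a test against zero when the true mean reduction is only 2.5** (SD 4.68, t test). The probability of a significant result is 79.3% at 29 and 80.7% at 30 (82.0% and 83.3% by normal approximation). The SD comes from amisulpride-treated patients and need not apply here. At n = 30 the probability is about 97% with SD 3.5 and 60% with SD 6.

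**Dropout.** 29 / 0.75 = 38.7, so 39; 30 / 0.75 = 40. Enrolling 40 agrees with the 30-completer target, so that step is sound.

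**The case against.** The strongest reply is that the figures can be derived from the stated inputs. The two-group formula with 5.98 − 2.5 gives 29 exactly, treats 2.5 as background to subtract, and fits the statement that the effect estimates were used. This stands, and it defeats one tempting inference: that 2.5 must have been the effect to detect and that 5.98 played no part. The numbers cannot tell the two routes apart. It does not rescue the calculation, because a one-armed trial has no second group. The 46 historical patients received amisulpride, so they cannot supply a group showing only the trial effect.

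A second reply is that the protocol nowhere specifies a test against zero. Its hypothesis is a response comparable to historical amisulpride, and the choice of test may sit in an analysis plan that is not shown. This also stands. A reader might infer that the trial as planned would pass an inert drug about 80% of the time. The document does not support that as a flat statement: it depends on a zero null that is never stated, and on borrowing the amisulpride SD.

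A third reply is that the Discussion says Sub-Sero is not pivotal and that a blinded randomised trial is needed. That limits the consequences. It does not make the printed inputs and results agree for one arm, and the results are meant to inform the design of later trials.

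**Conclusion.** The concern holds in this form: 29 completers and 95% power at 46 do not follow from a one-arm test of 5.98 against 2.5, which needs 15 to 17 patients and has 99.9% power at 46. The protocol does not say which calculation gave its figures, and neither of the two that come close is that test. The size of the trial is not the problem, since 30 completers are more than enough for the test against 2.5. What is left open is the null value, and with it the meaning of a positive result. The roughly 80% rate of significant results from a 2.5-point non-drug change is a warning about one possible choice of null, not a property of the plan as written. The recalculation assumes a two-sided 5% test and SD 4.68.

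**What to change.** 1. State how 29 was obtained: the test, its sidedness, the difference and the SD, and what role the 2.5 points play.
2. Set the primary comparison as the mean reduction against 2.5, with success requiring the lower limit of the two-sided 95% confidence interval to lie above 2.5.
3. Keep 30 completers and 40 enrolled. Restate power as about 98% at 30 for an expected 5.98 with SD 4.68, and, because 2.5 is itself an estimate, report that it is about 80% if the benchmark is 3.5.
4. Delete the 95% observed power for the amisulpride cohort.
5. If a different null was intended, such as 3.48 or a comparison with the amisulpride cohort, state it and give the matching calculation instead.

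The cost is rewording the sample-size and primary-endpoint paragraphs, with no added patients. The downside is a stricter criterion. With 30 completers and SD 4.68 the interval's half-width is 2.045 × 4.68 / √30 = 1.75, so the observed mean reduction would have to exceed about 4.25, compared with about 1.75 for a test against zero.

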### Hypotheses

Patients treated with pimavanserin in monotherapy will display a comparable response as patients treated with a conventional dopamine D2 antagonist (amisulpride). Observed response to 6 weeks of amisulpride treatment is shown in **Figure 1** and is based on comprehensive historical data from our group (**Figure 1**).Pimavanserin will be well-tolerated and induce fewer side-effects (e.g. fewer EPS, minimal weight gain and minimal hyperprolactinemia) than amisulpride (compared with historical data).Neurobiologically, we expect psychotic symptom reduction to be most prominent in the patients with the lowest frontal serotonin 2AR binding potential at baseline.Pimavanserin will produce improvements in measures of attention, verbal fluency, executive function, and working memory.Pimavanserin will exert non-detrimental effects on brain structure.

## Discussion

We anticipate that the Sub-Sero trial will contribute novel clinical and neuropsychiatric data from a cohort of antipsychotic-free, first-episode schizophrenia spectrum patients exposed to monotherapy with a selective 2AR antagonist.

The open-label study design of Sub-Sero is motivated by the fact that pimavanserin will be used off-label for a vulnerable group of antipsychotic-free, first-episode patients with schizophrenia spectrum disorder, who are challenging to recruit. Moreover, the current sparse level of evidence for efficacy of pimavanserin in this patient group remains to be demonstrated before embarking on a randomized controlled trial (RCT) design. Since clinical relevance is the highest priority in Sub-Sero, we chose psychotic symptom reduction as our primary outcome. We have no active control group, but the open label design permits us to compare treatment response with our previous cohorts, on which we have comparable and comprehensive data, e.g. see **Figure 1**.

Inherently, Sub-Sero should not be regarded a pivotal clinical trial. To truly estimate treatment effect of pimavanserin a double-blinded RCT is necessary. We argue that the burden of the disease in these vulnerable patients, along with the current insufficient treatment options justify this proof-of-concept trial with pimavanserin monotherapy.

We expect that Sub-Sero will provide unique information of the role serotonin 2AR in antipsychotic-free, first-episode psychosis, which may inform the design of future randomized clinical trials testing effectiveness of pimavanserin as monotherapy. If successful, Sub-Sero will aid identification of a “serotonergic subtype” of schizophrenia spectrum patients, thereby promoting the development of precision medicine for use in clinical psychiatric practice.

## Publication and Media

Positive and negative results will be published in international, scientific peer-reviewed journals, and data will be presented at national and international conferences.

